#### 9.2.2 Serious adverse events (SAEs)

A serious adverse event is any untoward medical occurrence or effect that at any treatment:

- results in death;
- is life threatening (at the time of the event);
- requires hospitalisation or prolongation of existing inpatients' hospitalisation;
- results in persistent or significant disability or incapacity;
- Any other important medical event that may not result in death, be life threatening, or require hospitalization, may be considered a serious adverse experience when, based upon appropriate medical judgement, the event may jeopardize the subject or may require an intervention to prevent one of the outcomes listed above.

*Procedures for handling the serious adverse events.*

The sponsor will report the SAEs through the web portal *ToetsingOnline* to the accredited METC that approved the protocol, within 15 days after the sponsor has first knowledge of the serious adverse events.

SAEs that result in death or are life threatening will be reported expedited. The expedited reporting will occur not later than 7 days after the responsible investigator

has first knowledge of the adverse event. This is for a preliminary report with another 8 days for completion of the report.

#### **9.2.3 Suspected unexpected serious adverse reactions (SUSARs)**

Not applicable.

### **9.3 Annual safety report**

Not applicable.

### **9.4 Follow-up of adverse events**

All AEs will be followed until they have abated, or until a stable situation has been reached. Depending on the event, follow up may require additional tests or medical procedures as indicated, and/or referral to the general physician or a medical specialist. SAEs need to be reported till end of study within the Netherlands, as defined in the protocol.

### **9.5 [Data Safety Monitoring Board (DSMB) / Safety Committee]**

Not applicable.

## 10. STATISTICAL ANALYSIS

General characteristics of dizzy and control participants will be described quantitatively. The data derived from questionnaires and the fall calendar will also be presented in a quantitative way. Missing data will be handled with multiple imputation analysis.

### 10.1 Primary study parameter(s)

#### I. Validation study

The external validity of our 7-item risk score will be quantified by assessing the reliability, discrimination and calibration of the model. The reliability of the model will be quantified with the Hosmer-Lemeshow goodness-of-fit statistic. We will assess the calibration of the model by plotting the predicted probabilities against the observed frequencies of persistent dizziness-related impairment. We will assess the discriminative ability of the model, i.e. its ability to distinguish dizzy patients with persistent dizziness-related impairment from dizzy patients without persistent dizziness-related impairment, by calculating the receiver operating characteristic curve (AUC). An AUC of 0.5 indicates no discrimination above chance, whereas an AUC of 1.0 indicates perfect discrimination. We will use R statistical software for bootstrapping to adjust for over-optimism in model performance.

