Several members of our research group initiated the study Dizziness In Elderly Patients (DIEP) in collaboration with the Department of General Practice of the Academic Medical Center Amsterdam in order to fill the gap of knowledge about dizziness in older patients. This study resulted in more knowledge of epidemiology, aetiology, and diagnosis of dizziness in older patients in general practice. Furthermore, a large cohort study investigating the prognosis of dizzy older patients in general practice recently identified seven risk factors for chronic dizziness with persistent impairment. These risk factors are (1) onset of dizziness more than six months ago, (2) dizziness provoked by standing still, (3) trouble with walking and/or falling as associated symptom, (4) polypharmacy, (5) absence of diabetes, (6) anxiety and/or depressive disorder, and (7) impaired functional mobility. Three

of these risk factors are amenable to treatment: polypharmacy, anxiety and/or depressive disorder, and impaired functional mobility.

The results of this cohort study, combined with previous findings of DIEP, provide the basis of the present research proposal.

The first objective of the proposed study is to externally validate our previously developed 7-item risk score for chronic dizziness with persistent impairment. Although the discriminative ability of our developed risk score was good (area under the receiver operating characteristic curve [AUC] of 0.80), it is necessary to validate prediction models in new individuals before they can be implemented in guidelines or applied in clinical practice. If our risk score confirms our previous findings, GPs will have an accurate, easy-to-use clinical tool to identify dizzy older patients with a poor functional prognosis.

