#### Validation study

The aim of the validation study is to validate a previously developed risk-score. This risk-score consists of 7 predictors and was constructed to predict the risk of chronic dizziness with persistent impairment (this means a DHI score  $\geq 30$  at 6 months follow-up).

A commonly used rule of thumb to judge sample sizes for developing diagnostic and prognostic models is the recommendation of at least 10 events per variable. This rule is based on estimates of the stability of coefficient estimates for individual variables in the model. According to this rule, at 6 months follow-up at least  $7 \cdot 10 = 70$  patients need to suffer from dizziness with a DHI-score  $\geq 30$  to enable validation of the risk-score. Based on secondary analysis of DIEP data we expect that 60% of the patients with a DHI  $\geq 30$  at baseline will have a DHI score of  $\geq 30$  at 6 months follow-up. Additionally to the validation of the previous developed risk score, we anticipate to model some 10-15 candidate variables to construct a new risk-score. With sample sizes of 125 patients in group A and 125 patients in group B we will be able validate the previous developed risk

score and we will be able to construct a new risk score with 15 predictors in impaired dizzy patients ( $0.6 * 250 = 150$ ,  $150/10 = 15$ ).

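### The only numerical check of predicted against observed risk is the Hosmer-Lemeshow test, which gives no size, direction or interval for miscalibration

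*Protocol*

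**What the plan says.** Section 10.1 (I. Validation study) splits external validity into reliability, discrimination and calibration, and gives each one tool.

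- Reliability: "The reliability of the model will be quantified with the Hosmer-Lemeshow goodness-of-fit statistic".
- Calibration: "We will assess the calibration of the model by plotting the predicted probabilities against the observed frequencies of persistent dizziness-related impairment".
- Discrimination: the area under the ROC curve.

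The section names no calibration intercept, no calibration slope and no interval for either. It also gives no number of risk groups, significance level or acceptance criterion for the Hosmer-Lemeshow statistic.

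Validation is the first primary objective (section 2). Section 1 says what is to follow from it for patients whose outlook is poor: "If our risk score confirms our previous findings, GPs will have an accurate, easy-to-use clinical tool to identify dizzy older patients". The only performance figure quoted there from development is an "area under the receiver operating characteristic curve [AUC] of 0.80".

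Section 4.4 (Validation study) justifies the sample size by 10 events per variable, which it introduces as a rule of thumb for developing models. Its conclusion on the score is: "With sample sizes of 125 patients in group A and 125 patients in group B we will be able validate the previous developed risk".

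**The concern.** Reliability in this sense means agreement between predicted and observed risk. A goodness-of-fit statistic cannot quantify it. A large value says that some disagreement exists. A small value says that none was detected, which may reflect good calibration or too few patients. Neither tells a reader whether the score overstates risk, is too extreme, or both.

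That distinction decides what to do next. A score that is off by a constant needs a new intercept. One whose predictions are too extreme needs its coefficients shrunk. The AUC cannot help, because it depends only on the ranking of patients. The plot helps the eye, but gives no number to report and no measure of its uncertainty.

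What is at stake is the strength of the claim that the tool is accurate, since section 1 presents validation as the step before use in guidelines and practice.

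**Working it through.** **Inputs from the protocol**

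- Validation sample: 125 + 125 = 250 (section 4.4).
- Event rate, DHI of at least 30 at 6 months: 60% (section 4.4).
- Predictors in the score: 7 (section 4.4). AUC at development: 0.80 (section 1).
- Loss to follow-up: 20%, stated for the intervention study only. Applied here as a sensitivity value, 0.8 × 250 = 200. Section 10 plans multiple imputation, so 250 may remain the analysed number.

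**Assumptions not in the protocol**

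- 10 equal risk groups and a 5% level.
- 10 degrees of freedom, because the score is applied unchanged and nothing is fitted.
- Normally distributed predicted log-odds with SD 1.4, which gives AUC 0.80 at 60% events. SD 1.0 stands for a narrower case mix.

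**The plan's own figures**

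7 × 10 = 70 events are needed; 0.6 × 250 = 150 are expected; 150/10 = 15 predictors. All three reproduce. None concerns the power or precision of a calibration measure.

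**Method**

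The true risk follows logit(p_true) = a + b × logit(p_pred). Two errors are examined:

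- slope error: b = 0.7, with mean risk held at 60%;
- overall error: b = 1, with a chosen so that true mean risk is 10 points below the prediction.

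The test statistic is Σ (O − E)² / [E(1 − E/n)] over the risk groups, referred to chi-square. The comparators are the calibration intercept (a, with b fixed at 1) and the calibration slope (b). Each misses the error when its 95% interval still contains 0 or 1 respectively. There were 3000 simulated trials per scenario.

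**Miss rates (1 − power)**

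| Scenario | HL, slope 0.7 | HL, 10 points too high | Intercept, 10 points too high | Slope interval, slope 0.7 |
|---|---|---|---|---|
| N = 250, SD 1.4 | 1 − 0.435 = 57% | 1 − 0.756 = 24% | 1 − 0.956 = 4% | 1 − 0.651 = 35% |
| N = 200, SD 1.4 | 1 − 0.361 = 64% | 1 − 0.640 = 36% | 1 − 0.920 = 8% | 1 − 0.566 = 43% |
| N = 200, SD 1.0 | 1 − 0.250 = 75% | 1 − 0.583 = 42% | 1 − 0.873 = 13% | 1 − 0.424 = 58% |

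A repeat of the first row gave about 57%, 26% and 5% in the first three columns, hence the rounded values of about 57%, 25% and 5%. The 95% half-width of the slope is about 0.24 to 0.33 over these scenarios.

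**Sensitivity of the Hosmer-Lemeshow miss rate**

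A second simulation left a at 0 when b changed, so that mean risk also drifts (by 2 points at slope 0.7). At N = 250, AUC 0.80 and 10 df:

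- slope 0.8: 76%; 0.7: 53%; 0.6: 24%; 0.5: 7%;
- risk overstated by 4.5 points: 83%; by 9 points: 35%.

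Other variations:

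- AUC 0.70, slope 0.7: 73%.
- 5 groups instead of 10 (first set-up, N = 250): 16% for the 10-point error; about 57%, unchanged, for slope 0.7.
- 8 df instead of 10 (second set-up, N = 250): 40% instead of 53% for slope 0.7. The chance of rejecting a perfectly calibrated score rises to about 11% (theory: P(χ² with 10 df > 15.51) = 0.115).

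Over the settings of the second simulation, the miss rate runs from 4% (slope 0.5, N = 250, 8 df) to 90% (slope 1.5, N = 200, 10 df).

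**The case against.** A reader might infer that the score will be declared reliable whenever the test is non-significant. The protocol does not say so. It states no level, cut-off or acceptance rule, and the sentence in section 1 about confirming previous findings follows a figure for discrimination, not calibration. That reading is not supported.

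A reader might also infer that calibration rests on this test alone. It does not. The plot is a planned, separate assessment, and a uniform 10-point overstatement is the kind of error it would display. What the plot lacks is an estimate and an interval.

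The miss rates can be challenged too. Group number, level, degrees of freedom and spread of risk are all assumed, and a 7-item score may take too few distinct values to form ten equal groups. This stands, and the rates should be quoted only with their assumptions.

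It can be added that the remedy detects a wrong slope only moderately better, since the slope interval itself misses 0.7 in 35% to 58% of cases. That is true. The gain there is that the uncertainty is reported.

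Finally, calibration statistics are often specified in a statistical analysis plan, which may exist. But the protocol does not leave the matter open: it names the tool that is to quantify reliability, and the tool cannot do so.

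**Conclusion.** The point holds as a limited criticism of a stated method. For a primary objective, the one numerical measure of agreement between predicted and observed risk is a test without an effect estimate, accompanied by a plot without an interval. With 250 patients, 60% events, AUC 0.80, 10 groups, 10 df and a 5% level, the test misses a slope of 0.7 in about 57% of cases and a 10-point overstatement in about 25%; the calibration intercept misses the latter in about 5%.

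No single miss rate is a property of this sample size, because the result changes with each assumption listed. Nor do the documents support a claim that the false-alarm rate will double. That would need 8 df to be applied to an unchanged score, and the protocol gives no degrees of freedom; with 8 df the miss rates would also be lower.

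Nothing here is a contradiction or a miscalculation. It is a poorer method where a better one is available at almost no cost.

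**What to change.** In section 10.1 (I. Validation study), replace the sentence on the Hosmer-Lemeshow statistic with wording such as: *Reliability will be quantified by the calibration intercept (calibration-in-the-large) and the calibration slope of the original score applied unchanged, each with a 95% confidence interval, presented beside the calibration plot.* If the Hosmer-Lemeshow statistic is kept, add: *It is reported descriptively; a non-significant result will not be taken as evidence of good calibration.*

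The work is one or two sentences and one logistic regression on data already collected. The drawback is that the slope will be known only to about ±0.24 to ±0.33, and a wrong slope can still go undetected. The report will show that limitation openly.

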#### II. Intervention study

We will perform both intention-to-treat and per-protocol analysis. We will use univariate and multivariate analyses to compare outcomes of usual care and intervention group. To investigate the effectiveness of the risk factor-guided intervention, we will use a repeated-measures mixed-effect (RMME) model to assess differences in the 1-year DHI score change, adjusted for potential confounders.

### 10.2 Secondary study parameter(s)

Presence of anxiety/depression, quality of life, dizziness frequency, fall incidence and health care utilization will be taken along in the univariate and multivariate analysis as stated above.

The economic evaluation will be analysed according to the intention-to-treat principle. Costs typically have a highly skewed distribution. Therefore, bootstrapping with 5000 replications will be used to calculate 95% confidence intervals around the mean difference in total costs between the treatment groups. The effect measure that will be used for the cost-effectiveness is EQ-5D-5L. Incremental cost-effectiveness ratios (ICERs) will be calculated by dividing the difference in mean total costs between the

treatment groups by the difference in mean effects between the treatment groups. Bootstrapping will be used to estimate the uncertainty surrounding the ICERs which will be graphically presented on cost-effectiveness planes. Cost-effectiveness acceptability curves and net monetary benefits will also be calculated. Cost-effectiveness acceptability curves show the probability that the intervention is cost-effective in comparison with usual care for a range of different ceiling ratios thereby showing decision uncertainty.

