### Secondary Objectives:

1. To investigate if a targeted intervention in older dizzy patients in general practice will reduce dizziness frequency and fall incidence.
2. To assess if health care utilization of older dizzy patients receiving a targeted intervention will decrease compared to older dizzy patients receiving usual care.
3. To investigate if our targeted intervention is cost-effective.
4. To investigate if older dizzy patients with significant dizziness-related impairment have more often an anxiety- or depressive disorder than non-impaired older dizzy patients in general practice.
5. To investigate the course of anxiety and depression in older dizzy patients in general practice during one year of follow-up.

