#### 8.1.2 Secondary study parameters/endpoints (if applicable)

- Quality of life, as measured with the EQ-5D-5L.
- Dizziness frequency, defined as the number of episodes of dizziness per day, week, month and year. Dizziness frequency will be assessed using a calendar filled in by the patient during a 12 month period.
- Difference in FRID count, defined as the difference in FRID count between baseline and after 12 months follow-up.
- Presence of anxiety/depression, as measured with GAD-7, PHQ-PD, and PHQ-9.
- Fall frequency, defined as the number of falls per year. Fall incidence will be assessed using a calendar filled in by the patient during a 12 month period.
- Health care utilization. We will use the extracted data from the electronic medical records of all patients to assess the number of registered medical consultations, prescriptions, referrals, hospital admissions, and nursing home admissions.

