### 8.3 Study procedures

#### Questionnaires

If a patient agrees to participate in the study he/she will receive a set of questionnaires. Patients in group A (n = 125) will receive three questionnaires at baseline and at 6 and 12 months follow-up. Patients in the intervention study (group B and C, n = 250) will receive four questionnaires at baseline and at 3, 6 and 12 months follow-up. The questionnaires will be discussed later in this section.

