### Outcome measures

#### Questionnaires

- Dizziness handicap inventory (DHI).

Time to fill out: 10 minutes.

The DHI is a widespread used self-report questionnaire, designed to quantify the impact of dizziness on everyday life. The DHI has 25 items with 3 answer categories ('yes', 'sometimes', or 'no'), investigating self-perceived physical, emotional, and functional disability associated with dizziness. DHI scores range from 0-100. A higher DHI score indicates a higher level of dizziness-related impairment. A DHI score of  $\geq 30$  correlates with current significant impairment because of dizziness.

- Dizziness handicap inventory, short version (DHI-S).

This is a short screening version of the DHI, in which 10 items of the original DHI are extracted. The 10 items in the DHI-S are scored are also scored in 3 answer categories ('yes', 'sometimes', or 'no'). A DHI score of  $\geq 12$  correlates with current significant impairment because of dizziness.

- Generalised Anxiety Disorder-7 (GAD-7).

Time to fill out: 5 minutes.

The GAD-7 is a 7-item questionnaire to identify GAD. Scores on the GAD-7 range from 0 to 21; scores of 5, 10, and 15 represent mild, moderate, and severe anxiety symptoms, respectively.

- Patient Health Questionnaire, panic module (PHQ-PD).

Time to fill out: 5 minutes.

The PHQ-PD will enable us to determine the presence of PD. The diagnostic algorithm for PD consists of 15 questions with 2 answer categories (yes or no) and is considered fulfilled if the answer to questions 3a-d is "yes" and if the answer to 4 or more of questions 4a-k is "yes".

- 9-item Patient Health Questionnaire depression module (PHQ-9).

Time to fill out: 5 minutes.

The PHQ-9 is designed to detect depression. The PHQ-9 has 9 questions with a score ranging from 0 to 3 for each question (maximum score of 27). A threshold score of 10 or higher is considered to indicate mild MDD, 15 or higher indicates moderate MDD, and 20 or higher severe MDD.

- Euro Quality of Life–5-dimension, 5-level (EQ-5D-5L).

Time to fill out: several minutes.

The EQ-5D-5L is a questionnaire that defines health in five dimensions (mobility, self-care, usual activities, pain/discomfort, anxiety/depression) and is often used to translate the effect of an intervention into Quality Adjusted Life Years (QALY's).

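### The anxiety/depression secondary outcome is reduced to presence or absence although PHQ-9 and GAD-7 totals are collected at every visit of the intervention study, so severity information is lost

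*Protocol*

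**What the plan says.** Section 8.1.2 lists the secondary outcome as "Presence of anxiety/depression, as measured with GAD-7, PHQ-PD, and PHQ-9". Section 10.2 carries the same variable into the comparison of arms: "Presence of anxiety/depression, quality of life, dizziness frequency, fall incidence and health care utilization will be taken along in the univariate and multivariate analysis".

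Section 8.3 (Outcome measures) describes the instruments. For the GAD-7: "Scores on the GAD-7 range from 0 to 21; scores of 5, 10, and 15 represent mild, moderate, and severe anxiety symptoms, respectively". The PHQ-9 has nine items scored 0 to 3, a maximum of 27, and severity thresholds at 10, 15 and 20. The PHQ-PD is a yes/no algorithm without a severity score.

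Patients in groups B and C "will receive four questionnaires at baseline and at 3, 6 and 12 months follow-up", and the measurement table in section 8.3 marks PHQ-9, GAD-7 and PHQ-PD at all four times for the intervention study.

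Secondary objective 5 is "To investigate the course of anxiety and depression in older dizzy patients in general practice during one year of follow-up". Secondary objective 4 compares how often impaired and non-impaired patients have a disorder. No section names a PHQ-9 or GAD-7 score, or its change, as an outcome to be compared between arms.

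**The concern.** Two graded scales and one binary algorithm are collapsed into a single yes/no status. A patient whose PHQ-9 falls from 22 to 11 is still above the threshold of 10 and counts as unchanged. A patient with depression resolved but panic disorder persisting also counts as unchanged.

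The protocol uses status to decide who is offered stepped care and when a patient moves to the next step (section 5.1). That use does not oblige the arm comparison to be binary. The protocol follows the opposite rule for its primary outcome: the DHI has a cut at 30 for eligibility, yet sections 8.1.1 and 10.1 analyse DHI score change as a continuous quantity in the intervention study and dichotomise only for the validation study.

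At stake is a secondary outcome close to the stepped-care component. Section 5.1 expects only 48% of the intervention group to be eligible for that component, so the contrast between arms is already diluted. Objective 5 would also have no severity trajectory.

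**Working it through.** **Inputs from the protocol.** Sections 4.4 and 5.1 give: DHI difference 12, SD 19.9, two-sided alpha 0.01, power 90%, cluster size 5, ICC 0.05, loss 20%, and 48% eligible for stepped care.

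**The plan's own figure.** n = 2(2.58 + 1.28)² × 19.9²/12² = 81.9, so 82. Design effect 1 + 4 × 0.05 = 1.2; 82 × 1.2 = 98.4, so 99. With 20% loss, 99/0.8 = 123.75, so 124. All three figures reproduce. (Separately, the bracketed line in section 4.4 prints 1.64 and 19.92 where 1.28 and 19.9 produce the 82; as printed it gives about 98.) Effective size per arm after loss and clustering is 99/1.2 = 82.5, taken as 82.

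**Assumptions, because the protocol gives none for this outcome.** Alpha 0.05, the same ICC as for the DHI, an approximately normal score, one follow-up time point, and a baseline-to-follow-up correlation of 0.6 where baseline adjustment is used.

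**Step 1: one score cut once.** Relative efficiency of the yes/no version is φ(c)²/[p(1 − p)], where c is the normal quantile of 1 − p.
- p = 0.48: 0.398²/0.2496 = 0.636.
- p = 0.30: 0.348²/0.21 = 0.576.
- The maximum, at p = 0.50, is 0.637, so the loss for a normal score is never below 36%.

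**Step 2: a uniform shift of d SD, no baseline adjustment.** Power of the score is Φ(d√(82/2) − 1.96). For d = 0.4 this is Φ(2.56 − 1.96) = 73%. The same shift takes presence from 48% to 32.6%, for which a two-proportion test has 52% power. For d = 0.3 the pair is 48% against 33%; for d = 0.5 it is 89% against 70%.

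**Step 3: the composite.** The protocol's 48% is not the share above one cut. It is the share positive on any of GAD, panic disorder or MDD. Simulations used 82 per arm, with effects of 0.4/0.6/0.8 SD in baseline-positive patients only. They compared covariance analysis of one score with logistic regression of status adjusted for baseline status. Composite runs used two correlated scores with 48% positive on either, panic omitted.

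| Scenario | Score, power % | Status, power % | Gain, points |
|---|---|---|---|
| One score cut at 48% | 35/60/84 | 22/42/62 | 13/18/22 |
| Composite, benefit only on the positive scale, scales correlated 0.5 | 18/33/55 | 18/31/50 | 0/2/5 |
| Same, scales correlated 0.7 | 22/38/61 | 17/32/48 | 5/6/13 |
| Composite, both scales improve | – | – | about 10 to 17 |

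The composite rows rest on 800 trials per setting. The standard error of a power near 50% is √(0.25/800) = 1.8 points, so single entries are approximate. Repeat runs gave 0 to 8 points when benefit is confined to the positive scale and 7 to 20 points when both scales improve.

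**Step 4: price of two outcomes.** If alpha is shared (0.025 each), score power in Step 2 for d = 0.3/0.4/0.5 falls from 48/73/89% to 37/63/83%.

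**The case against.** The strongest reply is that the loss is smaller than it looks. A reader might infer from Steps 1 and 2 that presence costs 10 to 20 points of power as a matter of fact. The documents do not support that. Those steps cut a single score, whereas the protocol's status combines three instruments and can pick up benefit on any of them. If benefit is confined to the scale on which the patient was positive and the scales are only moderately correlated, one score may gain almost nothing. This part of the objection stands.

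Some further points also stand:
- A PHQ-9 fall from 10 to 9 is not necessarily recovery, because GAD-7 or PHQ-PD may still be positive.
- Status at four visits does describe a course (onset, remission, persistence). What it lacks is severity.
- Secondary objective 4 needs disorder status.
- Stepped care ends, among other ways, when the patient no longer has anxiety or depression, so remission is a meaningful quantity.
- The EQ-5D-5L has an anxiety/depression dimension, so this is not the only outcome that bears on the stepped-care component.

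It can also be said that the coding is not settled. The summary lists only anxiety/depression, section 10.2 names no binary model, and a statistical analysis plan that is not shown might add score analyses. That carries less weight, because sections 8.1.2 and 10.2 agree on presence.

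**Conclusion.** The point holds in a limited form. The protocol names presence as the between-arm outcome in two places, while graded totals from two of the three instruments are already collected at all four times in both arms. Severity information is discarded for no stated reason, and against the protocol's own practice for the DHI.

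The size is conditional. Relative efficiency is about 0.64 for a single roughly normal score cut at 48% positive. Against the composite, the gain per score is about 0 to 20 points of power at 82 effective patients per arm and alpha 0.05. The 48% is a baseline share; if fewer patients are positive at follow-up, the single-score efficiency of the cut drops further (0.576 at 30%).

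This concerns one secondary outcome. The objectives that explicitly set intervention against usual care do not name anxiety or depression, and the primary DHI conclusion is untouched.

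**What to change.** In sections 8.1.2 and 10.2, make the PHQ-9 total and the GAD-7 total the analysed between-arm outcomes. Fit each in the same repeated-measures mixed model as the DHI, over 3, 6 and 12 months, with the baseline score as covariate. Use the same score trajectories for secondary objective 5. Keep presence of GAD, panic disorder or MDD as a supportive outcome and for secondary objective 4. The PHQ-PD stays binary.

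This changes wording only; every score is already scheduled. The downside is two score results in place of one composite result, with the power loss shown in Step 4 if alpha is shared between them. The text should say whether it is.
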